#### 2.2.2. Sample Size

The number of subjects is evaluated on the basis of detecting significant differences in the primary outcome, mean change of TNSS before and after medication among the groups with AR patients. In an earlier clinical study that evaluated other herbal medicines compared with placebo, the difference in TNSS was reported to be 0.97 with a standard deviation of 1.3 [14]. With a power of 80% (1–*β*) and a significance level of 5% (*α*), the target sample size is 29 patients per group. Considering an assumed dropout rate of 20%, a total of 105 subjects (35 subjects per group) will be required. Similarly, the number of subjects in previous exploratory phase II trials ranged from 20 to 42 per group [26–28].

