## 2. Methods/Design

### 2.1. Study Design

This study is a randomized, double-blind, placebo-controlled, phase II trial to evaluate the efficacy and safety of BJIGT for PAR. The trial will be conducted at the Daejeon University Daejeon Korean Medicine Hospital in Korea. We followed the methods of Lee et al. [25].

A total of 105 participants will be recruited for this trial and randomly assigned to a high-dose BJIGT group, standard-dose BJIGT group, or control group (placebo) in a 1 : 1 : 1 allocation ratio. The trial will consist of a 1-week run-in period after screening and a 4-week treatment period. Participants will take medications three times a day for 4 weeks, with visits at 2-week intervals; the detailed study design is summarized in Figure 1 and Table 1.

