### 2.7. Statistical Analysis

An independent statistician will analyze the data using SAS Analytics Pro. A full analysis set (FAS) is defined as the analysis based on intention-to-treat (ITT) principles, including the subjects who received at least one trial intervention when evaluating effectiveness. In this trial, efficacy evaluation will be primarily based on ITT analysis, and per-protocol (PP) analysis will be applied as a secondary analysis, including the subjects completing the entire trial without violating the protocol.

The demographic characteristics and baseline data will be expressed as means and standard deviations (SD) for continuous variables, and frequencies and percentages for categorical variables. The baseline differences between groups will be compared using an independent *t*-test for continuous values and the *χ*^2^ test or Fisher's exact test for categorical values. The efficacy outcome measures and the mean differences of TNSS from baseline to the treatment period will be analyzed by analysis of covariance (ANCOVA) with baseline data as a covariate for linear mixed models (LMMs). The baseline data are defined as the mean TNSS per day in the run-in period and will be compared with the diary-based mean TNSS for the 2-week treatment period or 4-week treatment period. The efficacy analysis methods are the same for TNSS by PI and Sasang constitution, KARQLQ, and biomarkers. The overall assessment of AR after the trial will be analyzed using a general linear model. All analyses will be set at a 5% significance level.

Safety evaluation will be conducted in the subjects who took one or more interventions, and the investigator will confirm at least one safety-related data set by visit or call after the intervention. A comparison of the number of AEs related with the trial will be conducted using the Kruskal–Wallis test, and group comparisons of the proportion of subjects who experienced one or more AEs will be analyzed using Pearson's *χ*^2^ or Fisher's exact test.

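### 35 per group less the assumed 20% dropout leaves 28, one below the plan's own target of 29 per group

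*Protocol article*

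**What the plan says.** Section 2.2.2 takes its inputs from an earlier trial of other herbal medicines against placebo, in which "the difference in TNSS was reported to be 0.97 with a standard deviation of 1.3". From these it concludes: "With a power of 80% (1–*β*) and a significance level of 5% (*α*), the target sample size is 29 patients per group". The next sentence makes the allowance for dropout: "Considering an assumed dropout rate of 20%, a total of 105 subjects (35 subjects per group) will be required". The inflation formula is not printed. Section 2.1 confirms equal allocation to the three groups, so 105 in total is 35 in each. Section 2.7 sets a 5% significance level without stating sidedness, makes the intention-to-treat analysis primary for efficacy, and makes the per-protocol analysis of completers secondary.

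**The concern.** A dropout rate is a share of those randomised. The number to randomise is therefore the evaluable target divided by the share expected to stay. Multiplying the target by one plus the rate gives a smaller number and leaves the trial short if the assumed rate occurs. Here the target of 29, the 20% rate and the 35 per group are printed together, and they do not fit: the sentence claims a protection against dropout that 35 per group does not give. A reader who relies on it would expect 29 evaluable patients per group at the assumed rate, where the expected number is 28.

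**Working it through.** **Inputs**, all from the protocol article: difference 0.97, SD 1.3, power 80%, significance level 5%, target 29 per group, dropout 20%, and 35 per group or 105 in total (section 2.2.2); allocation 1:1:1 (section 2.1). I assume a two-sided test, because that reproduces the plan's figure and a one-sided test does not.

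**Step 1: reproduce the target.** For two means by the normal approximation,

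n = 2 x [SD x (z for 1 − α/2 + z for power) / difference]²
= 2 x [1.3 x (1.960 + 0.842) / 0.97]² = 28.20, rounded up to 29.

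This matches the printed 29. A one-sided 5% test would give 23.

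**Step 2: reproduce the enrolment figure.**
- 29 x (1 + 0.20) = 34.8, rounded up to 35 per group; 3 x 35 = 105. This matches.
- 29 / (1 − 0.20) = 36.25, rounded up to 37 per group; 3 x 37 = 111. This does not match.
- Unrounded requirement: 28.20 / 0.80 = 35.24, which gives 35 only if rounded down.

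**Step 3: what remains after 20% dropout.**

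| Randomised per group | Remaining at 20% dropout | Against 29 |
|---|---|---|
| 35 | 28.0 | one short |
| 36 | 28.8 | just short |
| 37 | 29.6 | met |

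Over three groups, 105 x 0.80 = 84, against 3 x 29 = 87.

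**Step 4: dropout that 35 per group can absorb.** 1 − 29/35 = 6/35 = 17.1%.

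**Step 5: cost in power**, by the formula of step 1:
- 28 per group: 79.7%
- 29 per group: 81.1%
- 35 per group: 87.7%

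The shortfall costs 81.1 − 79.7 = 1.4 percentage points. By t-test the powers at 28 and 29 are 78.3% and 79.7%, again a difference of 1.4 points.

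**The case against.** The strongest reply is that almost nothing turns on this. By the formula that gave 29, power with 28 per group is 79.7%, which rounds to the stated 80%; against the unrounded requirement of 28.20 the shortfall is 0.2 of a patient per group. The primary analysis set includes everyone who received at least one intervention, and symptom scores are recorded twice daily, so someone who leaves after starting treatment may still contribute. If all 35 per group did, power would be 87.7% on the stated inputs. The planned baseline adjustment is not credited in the calculation either. This is a phase II trial, and section 2.2.2 sets its size beside exploratory trials of 20 to 42 per group.

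All of that stands as to size. It does not rescue the sentence. An allowance for dropout treats dropouts as lost to the calculation, and on that premise 35 does not deliver 29. The per-protocol analysis, which takes completers only, bears the loss in full. The range of sizes in earlier trials supports 35 as a reasonable number, but not as cover for 20% dropout from 29.

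A reader might infer three stronger things that the document does not support.
- *That the plan is shown to have multiplied by 1.2.* The figure fits, but no formula is printed, and dividing 28.20 by 0.8 and rounding down also gives 35. Either route leaves 28.
- *That dropout lowers power from 80% to about 78%.* This sets the t-test figure for 28 against a target derived by the normal formula. By t-test the plan's own 29 already gives only 79.7%, so most of that apparent drop would be a matter of mixed formulas.
- *That the trial will probably miss its target because, at 20% dropout, a given group keeps at least 29 of 35 with a chance of only about 43%.* With 37 per group the chance is still only 69%. An allowance covers the expected loss and guarantees no number.

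**Conclusion.** The point holds as a small arithmetic inconsistency in section 2.2.2. At the assumed 20% dropout, 35 per group leaves 28, one below the stated 29; the total consistent with both figures is 111, six more than 105. The cost is about 1.4 points of power by the plan's own formula (79.7% against 81.1%), and it falls mainly on the per-protocol analysis. The stated power is missed only by a fraction of a point, so the document does not support calling the trial materially underpowered on this ground. The conclusion rests on three assumptions: dropout is a share of those randomised, the test is two-sided, and dropouts contribute nothing. The last is the premise of the plan's own allowance, but it is probably too strict for the primary analysis.

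**What to change.** Keep 105 and correct the sentence in section 2.2.2 in one of two ways:

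1. State that 35 per group retains 29 per group with up to about 17% dropout (6 of 35).
2. Keep the 20% rate and state that it leaves 28 per group, with 79.7% power by the same normal-approximation formula.

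Either costs one sentence and no extra enrolment; the stated protection becomes slightly less favourable. If the sponsor prefers to keep both the target of 29 and the 20% rate, the matching size is 37 per group, 111 in total, at a cost of six more participants.

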#### 2.2.3. Recruitment

Participants are being recruited through advertising, and posters will be displayed in the outpatient departments of the hospital and the website homepage of the hospital. The posters will contain simple explanations of the enrollment criteria, purpose of the study, intervention, and predictable adverse events. Written informed consent will be obtained ahead of enrollment at our hospital's clinical trial center, and participants can determine whether or not to participate in the trial.

### 2.3. Interventions

The participants will receive placebo for a 1-week run-in period and high-dose BJIGT or standard-dose BJIGT or placebo for the 4-week treatment period. BJIGT and placebo granules are sealed in aluminum bags, and the participants will be instructed to take two packets of medicine (5.0 g) with water three times per day after each meal. The dosage is determined to be 15 g per day for the high-dose BJIGT and 7.5 g per day for the standard-dose BJIGT according to the Korean Ministry of Food and Drug Safety (MFDS) approval and the pharmacologically active dose in expectorant effective tests [29].

The BJIGT to be used in this study is composed of dried brown granules, and the extract is allowed and controlled by the Korean MFDS. Hankookshinyak Corporation (Nonsan, Korea) manufactures the BJIGT and placebo in accordance with Korea Good Manufacturing Practice standards. A 2.5 g sample of BJIGT consists of ten medicinal herbs: Ginseng Radix 0.665 g, Atractylodis Rhizoma 0.665 g, Astragali Radix 0.665 g, Angelicae Gigantis Radix (0.5 g), Citri Unshius Pericarpium 0.335 g, Bupleuri Radix 0.335 g, Zizyphi Fructus 0.335 g, Glycyrrhizae Radix 0.25 g, Cimicifugae Rhizoma 0.165 g, and Zingiberis Rhizoma 0.085 g. The placebo does not include any of these active ingredients and is made of lactose, corn starch, caramel coloring, etc. Both granules had the same shape, weight, and color as gray brown.

The participants will record their symptoms twice daily—morning and evening—in their TNSS diary for a total of 5 weeks. To improve and evaluate compliance, participants will be requested to record their dosage and return the remaining medications at the third, fourth, and fifth visits. Additional therapeutic interventions for AR equivalent to the exclusion criteria of the protocol will not be permitted during the trial.

### 2.4. Outcome Measures

#### 2.4.1. Primary Outcome Measure

*TNSS*. The primary outcome in this study is the difference in the changes in TNSS before and after the medication among the three groups. TNSS is the most widely used outcome in patients with AR and evaluates symptoms of rhinorrhea, nasal congestion, nasal itching, and sneezing. Each symptom will be rated on a four-point severity scale (0 = no symptoms, 1 = mild, 2 = moderate, and 3 = severe), and the total score will range from 0 to 12. There are two types of TNSS: reflective TNSS (r-TNSS), which evaluates how they felt during the past 12 hours, and instantaneous TNSS (i-TNSS), which evaluates how they feel at the time of assessment [30]. Participants will record the r-TNSS and i-TNSS in the diary twice daily during the run-in period and study period. The baseline data will be the average of the symptom scores during the run-in period, and mean score changes for 4 weeks or 2 weeks compared with baseline will be analyzed.

#### 2.4.2. Secondary Outcome Measures

*KARQLQ*. Measurement of AR-specific quality of life (QOL) impairment is significant for the assessment of the burden and efficacy of treatment. We will use the Korean Allergic Rhinitis-Specific Quality of Life Questionnaire (KARQLQ), which is the validated QOL questionnaire for Korean AR patients that consists of 15 questions about activities, nasal symptoms, practical problems, and other symptoms with a 5-point scale [31]. The KARQLQ will be measured at the third, fourth, and fifth visits (weeks 0, 2, and 4).

*Total IgE and Eosinophil Count*. Total IgE and eosinophil counts will be examined at the third and fifth visits (weeks 0 and 4) to assess the impacts of BJIGT on allergic and inflammatory responses. BJIGT has been demonstrated to have antiallergic and anti-inflammatory effects in animal studies and several clinical studies [18, 21].

*Overall Assessment of Allergic Rhinitis*. The overall degree of symptom changes for AR will be evaluated after treatment (fifth visit, week 4). The following scoring method will be used: 0 = very much improved, 1 = much improved, 2 = slightly improved, 3 = no change, 4 = slightly worse, 5 = much worse, and 6 = very much worse [32].

*Pattern Identification Questionnaire for AR*. To seek a more precise use of BJIGT, we will use the pattern identification (PI) questionnaire for AR based on a traditional Korean medicine perspective. The PI questionnaire for AR V.3.0 was developed by specialists in the Department of Otolaryngology of Korean medicine [33]. This questionnaire sorts patients with AR as possessing lung-heat, lung-cold, or spleen qi deficiency using the nasal symptoms and general conditions of AR patients.

*Sasang Constitution*. The Sasang constitution system by constitutional typology in Korean medicine differentiates individuals into four constitutional types. We will use the revised questionnaire for the Sasang Constitution Classification (QSCC II+) to refer to the differences in the effects of the Sasang constitution [34].

#### 2.4.3. Safety Assessment

Safety will be assessed through laboratory examinations, vital signs, and adverse events (AEs). To observe the safety of the participants, complete blood cell counts, blood coagulation test, blood chemistry examination (liver and kidney function test), serum hepatitis test, and urine test will be conducted at screening and at the fourth and fifth visits. The investigator will check vital signs and any unexpected or expected AEs at every visit and record details on a case report form (CRF). If serious AEs occur, the investigator will promptly stop the subject from taking medication and report it in accordance with the guidelines of the IRB.

### 2.5. Assignment of Interventions

#### 2.5.1. Allocation

The randomized allocation sequence will be produced by an independent statistician using SAS version 9 statistical software (SAS Institute, Cary, NC). The subject who meets the criteria will be given an identification code (random assignment number) with the same allocation ratio of 1 : 1 : 1 for a high-dose BJIGT, standard-dose BJIGT, or placebo group. The statistician will keep the randomization table separately until the blinding of the trial is maintained. The assignment is planned according to the assignment table created by a random assignment method that can be specifically designed and reproduced in advance. The statistician manages the assignment table, and the file is kept closed-door.

#### 2.5.2. Blinding

The subjects will be assigned to a random number and receive the medication package corresponding to the participant's identification code. Because this trial is double-blind, the participants or investigators will not be conscious of group assignment until the trial is ended. Removal of blindness will only be allowed in cases of serious medical emergencies.

### 2.6. Data Management and Monitoring

The investigators will obey the standard procedures of the trial. The investigators who assess outcome measures should be regulated to physicians who have attended training meetings. Data collection will be conducted at every visit for all groups. Collected documents and data on CRFs will be handled by only the principal investigator or those who are permitted to access the data. The investigator should preserve a copy of all clinical trial-related reports, the subjects' records, consent, and case records for at least three years after the end of the trial in a controlled-access laboratory archive.

Clinical trial monitoring will be performed via regular visits and occasional telephone calls by a clinical research associate (CRA) once or twice monthly. The CRA will confirm whether the trial is being executed in compliance with the protocol, and AEs are being appropriately reported and recorded on CRFs. The monitor will inspect the entire process of the clinical trial, and matters will be discussed with the investigator as and when they appear.

### 2.7. Statistical Analysis

An independent statistician will analyze the data using SAS Analytics Pro. A full analysis set (FAS) is defined as the analysis based on intention-to-treat (ITT) principles, including the subjects who received at least one trial intervention when evaluating effectiveness. In this trial, efficacy evaluation will be primarily based on ITT analysis, and per-protocol (PP) analysis will be applied as a secondary analysis, including the subjects completing the entire trial without violating the protocol.

The demographic characteristics and baseline data will be expressed as means and standard deviations (SD) for continuous variables, and frequencies and percentages for categorical variables. The baseline differences between groups will be compared using an independent *t*-test for continuous values and the *χ*^2^ test or Fisher's exact test for categorical values. The efficacy outcome measures and the mean differences of TNSS from baseline to the treatment period will be analyzed by analysis of covariance (ANCOVA) with baseline data as a covariate for linear mixed models (LMMs). The baseline data are defined as the mean TNSS per day in the run-in period and will be compared with the diary-based mean TNSS for the 2-week treatment period or 4-week treatment period. The efficacy analysis methods are the same for TNSS by PI and Sasang constitution, KARQLQ, and biomarkers. The overall assessment of AR after the trial will be analyzed using a general linear model. All analyses will be set at a 5% significance level.

Safety evaluation will be conducted in the subjects who took one or more interventions, and the investigator will confirm at least one safety-related data set by visit or call after the intervention. A comparison of the number of AEs related with the trial will be conducted using the Kruskal–Wallis test, and group comparisons of the proportion of subjects who experienced one or more AEs will be analyzed using Pearson's *χ*^2^ or Fisher's exact test.

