**Methods:**

This is a randomized, double-blind, placebo-controlled, phase II trial. A total of 105 patients, identified with perennial allergens, with a history of PAR and a mean total nasal symptom score (TNSS) ≥ 5 during the run-in period will be recruited from Daejeon Korean Medicine Hospital. Participants will be randomly assigned to a high-dose BJIGT group, standard-dose BJIGT group, or control group (placebo) in a 1 : 1 : 1 allocation ratio after a week run-in period. The treatment medication will be taken three times per day for 4 weeks. The primary outcome measure is the mean change in the TNSS before and after medication. The secondary outcome measures include the Korean Allergic Rhinitis-Specific Quality of Life Questionnaire, total IgE and eosinophil count, overall assessment of AR, pattern identification questionnaire for AR, and Sasang constitution. *Discussion*. The aim of this study is to investigate the efficacy and safety of BJIGT in the treatment of PAR and to determine the suitable dosage of BJIGT. Therefore, we planned a randomized, controlled, phase II trial of two different doses of BJIGT compared with placebo, and the results of this study are expected to provide evidence for the use of BJIGT as a treatment of PAR. Trial Registration. The National Clinical Trial Registry Clinical Research Information Service, CRIS, KCT0006616, https://cris.nih.go.kr/cris/search/detailSearch.do/20706.

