## Figures and Tables

**Figure 1 fig1:**
[figure not shown]
Flowchart of the study plan. BJIGT, Bojungikgi-tang.

**Table 1 tab1:** Schedule of enrollment, interventions, and outcome measurements.

Time point, wk	Screening	Run-in period	Study period		
	−2 W	−1 W	0 W	4 W	8 W
Visit	1	2	3	4	5
Enrollment					
Informed consent	X				
Eligibility screen	X	X			
Allocation			X		
Demographic characteristics	X				
Medical history	X				
Chest X-ray, EKG	X				
Vital signs	X	X	X	X	X

Interventions					
Prescription		X	X	X	
High-dose BJIGT					
Standard-dose BJIGT					
Placebo					

Assessments					
Clinical laboratory test^(1)^	X			X	X
Pregnancy diagnosis test	X				X
MAST	X				
TNSS					
KARQLQ			X	X	X
Biomarkers^(2)^			X		X
Overall assessment					X
Pattern identification			X		
Sasang constitution			X		
Compliance			X	X	X
Adverse reaction assessment		X	X	X	X

(1) complete blood cell count tests, blood coagulation test, blood chemistry examination (liver and kidney function test), serum hepatitis test, and urine analysis; (2) total IgE, eosinophil count. BJIGT, Bojungikgi-tang; MAST, multiple allergen simultaneous tests; TNSS, total nasal symptoms score; KARQLQ, Korean Allergic Rhinitis-Specific Quality of Life Questionnaire.

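### Pattern identification and Sasang type are week-0 classifiers listed as secondary outcomes, and the analysis stated for TNSS by type does not, on its natural reading, test whether the effect differs by type

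*Protocol article*

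**What the plan says.** The Methods part of the abstract names, among the secondary outcome measures, "overall assessment of AR, pattern identification questionnaire for AR, and Sasang constitution". Section 2.4.2 (Secondary Outcome Measures) gives each its own entry. PI is included "To seek a more precise use of BJIGT" and sorts patients into three patterns. The Sasang questionnaire is included "to refer to the differences in the effects of the Sasang constitution" and sorts them into four types.

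Table 1 marks PI and Sasang constitution once each, at visit 3 (week 0), which is also the allocation visit. Neither is repeated. KARQLQ and the biomarkers, by contrast, are measured again after treatment.

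Section 2.7 describes the efficacy analysis as ANCOVA in a linear mixed model framework. Baseline is the only covariate named. It then states: "The efficacy analysis methods are the same for TNSS by PI and Sasang constitution, KARQLQ, and biomarkers". All analyses are set at the 5% level. The sample size in section 2.2.2 is for the overall comparison only: difference 0.97, SD 1.3, power 80%, 29 per group, raised to 35 for dropout.

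**The concern.** Two statements do not fit the design. First, a variable with no value after treatment starts cannot be an outcome of treatment. The purposes given in section 2.4.2 show that both classifications are meant as effect modifiers.

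Second, asking whether an effect differs between types calls for a comparison of effects across types. An ANCOVA of treatment repeated inside each type asks only whether treatment differs from placebo in that type. A significant result in one type beside a non-significant result in another is not evidence that the effects differ. With small types and a 5% level for every test, such a pattern is expected by chance, whether the treatment does nothing or works equally well in everyone. What is at stake is the reading of the secondary results, not the primary comparison.

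**Working it through.** **Inputs.** From section 2.2.2: difference 0.97, SD 1.3, power 80%, significance level 5%, 29 evaluable and 35 randomised per group. From section 2.4.2: 3 PI categories and 4 Sasang types. From section 2.7: 5% for every analysis.

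Assumptions: two-sided tests; equal-sized types, since the document gives no distribution; t-tests in place of baseline-adjusted ANCOVA; one TNSS score and one treatment period.

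**The plan's own figure.** n = 2(1.960 + 0.842)² × 1.3² / 0.97² = 28.2, rounded up to 29 per group. This matches the protocol. A one-sided test would give 23, so the two-sided assumption is the one that fits. The t-based power at 29 per group is 79.7%.

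**False positives when there is no effect in any type.**
- Seven three-group tests (3 + 4): 1 − 0.95⁷ = 30.2% if independent. PI and Sasang classify the same patients, so the tests are not fully independent. Simulation of 6,000 trials gives 29.1% with 29 per arm and 28.0% with 35.
- Each dose against placebo in each type, 7 × 2 = 14 tests: 1 − 0.95¹⁴ = 51.2% if independent. Simulation, which also allows for the shared placebo arm, gives 45.5% and 45.3%. Across variants of the t-test and arm size the range is about 44–47%.

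**Power within one type for a difference of 0.97** (noncentral t, noncentrality 0.97 / (1.3 × √(2/m)), m patients per arm in the type):

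| Evaluable per arm | Classifier | m | Power |
|---|---|---|---|
| 29 | PI | 29/3 = 9.7 | 34% |
| 35 | PI | 35/3 = 11.7 | 41% |
| 29 | Sasang | 29/4 = 7.25 | 26% |
| 35 | Sasang | 35/4 = 8.75 | 31% |

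**Chance that a uniform effect looks selective.** If the true difference is 0.97 in every type, the probability that one dose is significant against placebo in some types but not all is 1 − pᴷ − (1 − p)ᴷ, where p is the power within a type and K the number of types.
- PI, 29 per arm: 1 − 0.341³ − 0.659³ = 67%.
- PI, 35 per arm: 1 − 0.406³ − 0.594³ = 72%.
- Sasang, 29 per arm: 1 − 0.259⁴ − 0.741⁴ = 69%.
- Sasang, 35 per arm: 1 − 0.310⁴ − 0.690⁴ = 76%.

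**What interaction tests would offer.** Two tests at 5% give at most about 1 − 0.95² = 9.75% chance of any false positive if independent. Their power is low. The difference in effect between two types, for one dose against placebo, has standard error 1.3 × √(4/m). With 29 per arm, 80% power needs a difference in effect of 2.802 × 1.3 × √(4/9.67) = 2.3 points for PI and 2.802 × 1.3 × √(4/7.25) = 2.7 points for Sasang. For a difference in effect of 0.97, power is about 21% (PI) and 17% (Sasang). These last figures use the normal approximation and a single contrast between two types.

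**The case against.** The strongest reply is that section 2.7 does not literally describe separate models. TNSS by PI could mean one model with PI as a further factor, including its interaction with treatment. The same sentence also covers KARQLQ and the biomarkers, so it may name a family of methods and not a full model. Exploratory labels and multiplicity rules for secondary analyses are commonly left to the full protocol or analysis plan, and their absence from an article is no finding.

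Part of this stands. Repeating the ANCOVA within types is the natural reading but not the only one. Still, the sentence says the methods are the same, and the method described has no treatment-by-type term. If an interaction model is intended, the sentence needs correcting anyway. The outcome label is also stated outright, and Table 1 contradicts it, although section 2.7 itself uses both variables as classifiers.

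A reader might infer three stronger things that the document does not support:
- **That fourteen pairwise tests are planned.** The primary outcome is defined as a difference among three groups and no dose–placebo contrasts are specified, so the 44–47% figure is conditional and 29% is the figure for three-group tests.
- **That within-type p-values will decide who should receive BJIGT.** No such rule is stated, and the recommendation expected in the Discussion concerns dosage.
- **That the trial cannot show differential response at all, or is bound to yield chance findings.** The first holds only while no interaction is tested, and the second is a raised probability, not a certainty.

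It is also fair that an interaction test gains little power. Its merit is that it addresses the question asked.

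**Conclusion.** The point holds in this form. PI and Sasang type are baseline classifiers wrongly placed among the outcomes, and the analysis stated for TNSS by type does not, on its natural reading, compare effects between types. Under that reading the chance of at least one false positive is about 29%, or about 44–47% with dose-by-dose comparisons. A uniform effect of the planned size would look selective in roughly two thirds to three quarters of trials.

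These sizes rest on equal types and unadjusted t-tests at SD 1.3. Unequal types would lower power in the smallest ones, and baseline adjustment could raise it somewhat. The primary analysis and the sample size are unaffected.

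**What to change.** In the abstract and section 2.4.2, move PI and Sasang constitution out of the secondary outcomes and describe them as baseline effect modifiers. In section 2.7, replace the sentence on TNSS by type with one full-sample ANCOVA or mixed model containing a treatment-by-PI interaction and one containing a treatment-by-Sasang interaction. Report the type-specific differences from placebo with 95% confidence intervals, label them exploratory, and state that no conclusion will be drawn from within-type p-values.

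The change is to wording only and needs no new patients, visits or data. The drawback is the low power of the interaction tests at this size, so the results can only generate hypotheses and a non-significant interaction should not be read as proof of a uniform effect.
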